**Methods/design:**

Randomized, controlled, prospective, single-center clinical trial with duration of 12 months will be performed to compare the effect of Dader Method of pharmaceutical care with the usual care process of patients in a psychiatric clinic. Patients diagnosed with BD-I aged between 18 and 65 years who have been discharged or referred from outpatients service of the San Juan de Dios Clinic (Antioquia, Colombia) will be included. Patients will be randomized into the intervention group who will receive pharmaceutical care provided by pharmacists working in collaboration with psychiatrists, or into the control group who will receive usual care and verbal-written counseling regarding BD. Study outcomes will be assessed at baseline and at 3, 6, 9, and 12 months after randomization. The primary outcome will be to measure the number of hospitalizations, emergency service consultations, and unscheduled outpatient visits. Effectiveness, safety, adherence, and quality of life will be assessed as secondary outcomes. Statistical analyses will be performed using two-tailed McNemar tests, Pearson chi-square tests, and Student’s t-tests; a *P* value <0.05 will be considered as statistically significant.

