The intervention group patients will be monitored through the Dader Method for pharmaceutical care, over a 12-month follow-up period, to identify, prevent, and resolve drug-related problems with the process (causes) and drug-related problems with the outcome (effects). The strategy will consist of weekly phone calls and appointments with the patient, which, depending on the case, will take place at the patient’s home or at the pharmacist’s office. The pharmacist will inform the psychiatrist responsible for the patient in the case an effectiveness or safety problem related to the drugs is found, and the psychiatrist will determine the process to be followed.

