### Study outcomes

#### *Evaluation/assessment variables/measuring instruments*

The primary outcomes to be measured are: (1) the number of hospitalizations; (2) the number of emergency service consultations; and (3) the number of unscheduled outpatient visits. In addition to the information provided by patients and family members about the primary objective, the pharmacist gets the information from the records of medical history of the patients, provided by SJDC.

The secondary outcomes to be measured are: (1) adherence to treatment through serum lithium levels, serum valproate levels, carbamazepine-serum levels, and by the questionnaire of Morinsky-Green (MG) [21]; (2) life quality through the Quality of Life Scale: The Short Form (36) Health Survey Questionnaire [22]; (3) Clinical Global Impression for Bipolar Modified scale, CGI-BP-M [23]; (4) Young Mania Rating Scale for the evaluation of mania [24]; (5) Hamilton Rating Scale for Depression [25]; (6) drug safety through creatinine, liver transaminases, alkaline phosphatase, complete blood count, fasting glucose, thyroid stimulating hormone levels (TSH), total T4 or total thyroxin levels (T4), weight and cholesterol; (7) problems related to necessity, effectiveness, and security of the pharmacotherapy (NOMs to be identified and measured); (8) drug-related problems in drug therapy effectiveness, and safety; (9) the impact of side effects of antipsychotic drugs on health-related quality of life with a specific self-rated instrument: the ‘Tolerability and quality of Life’ (TOOL) questionnaire [26]; and (10) the patient’s satisfaction with the pharmaceutical care service measured through the patient satisfaction questionnaire on pharmaceutical care [27]. Control and intervention groups will be compared in terms of the proportion of changes from baseline to follow-up at 12 months. The information collected at 3, 6, and 9 months is part of the follow-up period of patients, and these data help to complement the secondary outcomes of the trial. Secondary outcomes will handled in terms of the proportion of changes from baseline to 12 months following.

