### Sample size calculation

The sample size and power were calculated using EpiInfo™ version 6.04 (Centers for Disease Control and Prevention, Atlanta, GA, USA). Assuming readmissions will be 50% in the control group and 30% in the intervention group, with a confidence of 95% and a power of 80%, it would be required to include at least 166 patients. The estimated sample size of 200 patients with a BD-I diagnosis is needed to cover losses during the follow-up and to increase sensitivity towards secondary objectives.

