### Biostatistical considerations

Data will be analyzed according to the intention-to-treat principle. All patients will be analyzing according to their allocated treatment group. Statistical analysis will be blinded and performed using SPSS version 13.0 (IBM SPSS, Armonk, NY, USA). Control and intervention groups will be compared in terms of the proportion of changes from baseline to 12 months following. Repeated-measures analysis will carry out. Clinical assessments will be made at baseline and every 3 months during the study period. Follow-up will be continuing to complete the year, even if a relapse or psychiatric hospitalization occurred. The main end points of interest are the number and duration relapse events per person-year of follow-up and number of admissions to the hospital due to BD. Data will be reported as means and standard deviations (SD) or as percentages. The Pearson chi-square test (between study groups) and the McNemar test (within-group changes from baseline to follow-up at 12 months) will be used to compare proportions. Comparisons for categorical variables will be conducted by using Chi-square tests (the Fisher exact test when appropriate) and for continuous variables by using the independent-sample t test (Mann-Whitney U test when appropriate). The Mann-Whitney test will be used to compare outcomes between groups. For quality-of-life questionnaire the Student’s t test will be used if sample distribution proves to be normal. Otherwise, the Wilcoxon rank-sum test will be used. The paired Student’s t-test (within-group changes from baseline to follow-up at 12 months) or the independent sample Student’s t-test (between study groups) will be used to compare means; odds ratios (ORs) and 95% confidence intervals (CIs) will be estimated as well. Mean number and duration of relapse events normalized to person-time, will be compared between groups using the Student’s t test. Multivariable analyses will be performed to explain the association of multiple variables associated with the factors significantly related to primary outcome: hospitalizations, readmission, relapse and total number of episodes of illness, number and total days of hospitalizations, days of illness, and days of free intervals per year. The sociodemographic and clinical variables to assess will be: duration previous episodes, severity of depression or mania, polarity of the last episode (manic, hypomanic, depressive, or mixed), co-morbid psychiatric illness, social support, psychosocial factors, educational level, living in rural area, having a history of violence to others, having no insight, non-compliance to medication, lack of practical support from the family. Analysis of depression and mania episodes, adherence to pharmacotherapy and quality of life will be performed, using repeated measure analysis. Comparisons will be analyzed using two-tailed tests, *P* <0.05 will be considered as statistically significant.

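### The outcomes section and the statistics section name different primary endpoints, only a readmission proportion is powered, and every comparison is judged at two-tailed 0.05

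*Protocol article*

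**What the plan says.** **Outcomes section.** Under Study outcomes the protocol article states "The primary outcomes to be measured are: (1) the number of hospitalizations; (2) the number of emergency service consultations". A third primary count covers outpatient visits that were not scheduled. The abstract lists the same three in the singular: "The primary outcome will be to measure the number of hospitalizations, emergency service consultations, and unscheduled outpatient visits". The aim in the Background, the descriptions of both study arms, the Figure 1 caption and the Discussion agree. Relapse appears in neither the primary nor the secondary list.

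**Statistics section.** Biostatistical considerations says "The main end points of interest are the number and duration relapse events per person-year of follow-up and number of admissions to the hospital", and then restricts those admissions to ones due to BD. It gives relapse number and duration per person-time their own Student's t test, and the Missing data section defines how both are calculated. Emergency consultations and unscheduled visits are not among these main end points.

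**Sample size.** The calculation uses a proportion: "Assuming readmissions will be 50% in the control group and 30% in the intervention group", with 95% confidence and 80% power. It gives at least 166 patients, raised to 200.

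**Threshold.** Biostatistical considerations applies two-tailed P<0.05 to all comparisons. The article states no composite, hierarchy, division of alpha or rule for success.

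**The concern.** Two statisticians working from this article could report different primary results from the same data. One would test three service-use counts. The other would test relapse number, relapse duration and BD admissions. Neither would be testing the quantity for which the trial was sized.

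Participants and pharmacist are unblinded, and the same pharmacist collects data in both arms. A headline endpoint that can be chosen from several lists, each traceable to the protocol, weakens whatever is claimed. With each candidate held to 0.05 and nothing said about how they combine, the text leaves open a claim of effectiveness on any one of them, at an error rate above the nominal level.

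**Working it through.** **1. The definitions side by side**

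| Item | Study outcomes | Main end points sentence | Sample size |
|---|---|---|---|
| Hospital admission | count, cause not stated | count, due to BD | readmission, as a proportion |
| Emergency consultations | primary | absent | absent |
| Unscheduled outpatient visits | primary | absent | absent |
| Relapse number per person-year | absent | main | absent |
| Relapse duration per person-year | absent | main | absent |

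Admission to hospital is the only concept present in all three columns, and it takes a different form in each.

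**2. The plan's own figure**

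Inputs from Sample size calculation: p1 = 0.50, p2 = 0.30, power 80%. Allocation is 1:1, from the 250 and 250 codes under Randomization. Per arm, n = [z_alpha·√(2·p̄·q̄) + z_beta·√(p1·q1 + p2·q2)]² / (p1 − p2)², with p̄ = 0.40, 2·p̄·q̄ = 0.48 and p1·q1 + p2·q2 = 0.25 + 0.21 = 0.46.

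- One-sided 0.05 with continuity correction: 83 per arm, **166** in total. Of the variants tried, only this one returns the stated figure.
- Two-sided 0.05: 93 per arm, 186 in total; with continuity correction 103 per arm, 206 in total.

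So 166 is a calculation for a difference in proportions, and it matches a one-sided 5% test rather than the two-tailed tests planned. The endpoint conflict does not depend on this, but it affects the power figures in step 4.

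**3. Familywise error if success on any one outcome counts**

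For k independent tests at 0.05 the rate is 1 − 0.95^k.

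- k = 3 (the three counts): 1 − 0.95³ = 0.143.
- k = 5 (adding relapse number and duration): 1 − 0.95⁵ = 0.226.

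The article gives no correlations between outcomes, so the other columns use equicorrelated normal test statistics at assumed values.

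| Outcomes | Independent | Correlation 0.5 | Correlation 0.8 |
|---|---|---|---|
| Three, either direction | 14.3% | 12.5% | 9.8% |
| Three, favouring the intervention (nominal 2.5%) | 7.3% | 6.3% | 4.9% |
| Five, either direction | 22.6% | 18.3% | 12.7% |

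BD admissions are not counted as a further candidate because they overlap with hospitalizations.

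**4. Power for the readmission comparison**

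Power = Φ{[0.20 − z·√(0.48/n)] / √(0.46/n)}, without continuity correction. With n = 100 per arm and no losses, the two roots are 0.0693 and 0.0678.

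- Two-sided 0.05: (0.20 − 1.960 × 0.0693)/0.0678 = 0.95, power **82.8%**.
- Two-sided 0.05/3 = 0.0167, the strictest Holm step: (0.20 − 2.394 × 0.0693)/0.0678 = 0.50, power **69.3%**.
- For 80% power at 0.0167: 125 per arm, 250 in total.
- At 83 per arm and two-sided 0.05: power 75.3%.

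**The case against.** The strongest reply is that the primary outcomes are not in general disorder. Nearly every section that names them gives the same three counts, and only the statistics section departs. Success rules and multiplicity are commonly left to an analysis plan, which is not shown here, and a journal article is condensed. All of this is fair. The absence of a success rule is therefore not the fault by itself. The contradiction between two sections of the same document is, and an analysis plan that is not shown cannot remove it. Relapse is also no stray word, because it has its own test and its own derivation.

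Four stronger readings might be inferred, and the documents do not support them.

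- **That the plan declares success on any one outcome.** It says nothing either way. The error rates above are conditional on that reading.
- **That there is a third rival set of primary endpoints.** The multivariable paragraph refers to "factors significantly related to primary outcome: hospitalizations, readmission, relapse and total number of episodes of illness" and further items. That sentence concerns factors associated with outcomes. It is poorly labelled but does not describe between-group confirmatory tests.
- **That hospitalization is all-cause in the outcomes section.** No cause is stated there. Unspecified is not the same as all-cause.
- **That the intervention itself generates unscheduled visits.** Under Intervention design, "The pharmacist will inform the psychiatrist responsible for the patient in the case an effectiveness or safety problem" is found, and the psychiatrist then decides what follows. No visit is stated, and fewer such visits is an explicit aim of the trial. Flagging visits triggered by a pharmacist's report would not help either, because such reports are described only for the intervention arm.

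**Conclusion.** The concern holds as a contradiction on the face of the article. The outcomes section and the statistics section share only hospital admission, defined differently in each, and the powered quantity is a third form of it.

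If any single success counts, the chance of at least one false-positive result among the three counts is about 10% to 14% over assumed correlations of 0.8 to 0. Counting only results in favour of the intervention, it is about 5% to 7% against 2.5%. Adding the two relapse measures raises the two-sided figure to about 13% to 23%. These sizes rest on the assumed correlations and on the any-one-success reading. The conflict of definitions rests on neither.

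**What to change.** **Preferred.** Make the proportion of patients with at least one hospital admission in the 12 months after randomization the single primary endpoint, tested two-sided at 0.05 by chi-square, a test the plan already names. Use one cause definition under Study outcomes, Sample size calculation and Biostatistical considerations. The wording at least one admission is safer than readmission because patients may also enter by outpatient referral. Make emergency consultations, unscheduled visits, relapse number and relapse duration secondary.

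**Alternative.** Keep the three counts as primary and test them with Holm at an overall two-sided 0.05. State how the powered readmission proportion relates to the hospitalization count.

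**In either case.** Amend the main end points sentence to match the outcomes section. Keep the multivariable list, but label it as the dependent variables of an explanatory analysis and not as the primary outcome.

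**Cost.** No new data are needed. The change must be made before anyone sees unblinded results, and the registration updated if needed. It is more than an edit of wording: the article puts the first randomization in November 2011, so data have already accrued in an open-label trial, and the amendment should be dated and explained. Under the preferred option, emergency and unscheduled visits lose primary status. Under the alternative, power for the readmission comparison at 200 patients with no losses falls from about 83% to about 69% at the strictest Holm step.

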### Data collection

Data will be collected from November 2011 to June 2013. The study will have a total length of 30 months, but time monitoring of each patient will last 12 months. The recruitment period will be 18 months, and patients will be evaluated during 12 months, starting from the date of their recruitment. Once the enrolment period ends, the final 12 months will be only used to evaluate the latest patients. However, for ethical considerations, all patients will be followed periodically by phone calls and further medical history review in the routine control appointment with the physician. Monitoring and evaluation of the variables related to the study (including questionnaires) will take place as follows: at baseline, which corresponds to the day of study entry, and every 3 months at the patients’ check-ups to complete the year of follow-up. The data obtained in this study will be registered in an electronic database that will include the Morinsky-Green questionnaire to measure medication adherence, the scale SF-36 Health Status Questionnaire to estimate quality of life, the Clinical Global Impression for Bipolar Modified (CGI-BP-M) scale to measure the assessing global of illness, the Young Mania Rating Scale for evaluating mania, and the Hamilton Depression Rating Scale to measure depression. Data regarding medication history, interviews with the pharmacist, health current status, plans of action will be registered as well. Related to the primary outcome, in addition to the information provided by patients and family members, the pharmacist gets the information from the records of medical history of the patients, provided by SJDC.

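### The arms are compared on readmission and hospitalization with unadjusted tests only, although mania and depression severity are scored at entry: valid, but an avoidable loss of efficiency and of protection against chance imbalance

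*Protocol article*

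**What the plan says.** The sample size rests on a binary outcome: "Assuming readmissions will be 50% in the control group and 30% in the intervention group". The test for proportions is fixed in Biostatistical considerations: "The Pearson chi-square test (between study groups) and the McNemar test (within-group changes from baseline to follow-up at 12 months) will be used". Fisher's exact test is the fallback. The section adds: "The Mann-Whitney test will be used to compare outcomes between groups". Relapse number and duration per person-time are compared by t test. None of these uses a covariate. On sidedness the section says: "Comparisons will be analyzed using two-tailed tests".

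The section also plans a separate model: "Multivariable analyses will be performed to explain the association of multiple variables associated with the factors significantly related to primary outcome". The outcomes it covers include hospitalizations and readmission. The variables to assess include "duration previous episodes, severity of depression or mania, polarity of the last episode" and, further down the list, non-compliance to medication. Randomized arm is not named as a term.

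Data collection puts the study variables, questionnaires included, at the day of entry and every three months. The database is to hold "the Young Mania Rating Scale for evaluating mania, and the Hamilton Depression Rating Scale to measure depression". Patient recruitment and group assignment has the study variables assessed before the patient is randomized. Randomization describes one list of 500 numbers, 250 per arm, with no strata.

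**The concern.** If severity at entry predicts readmission, an unadjusted test leaves that predictable variation in the error. A chance difference in severity between the arms then passes directly into the estimated effect, and nothing in the allocation scheme limits it. The remedy needs no extra patients and, for the two rating scales, no extra data.

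There is little power to spare. The 200 patients are meant to absorb losses, and the unadjusted two-sided test falls short of 80% if only 166 are analysed.

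**Working it through.** **Inputs from the protocol.** Readmission 50% control and 30% intervention; 95% confidence, 80% power, at least 166 patients; 200 recruited (Sample size calculation). Two-tailed tests at 0.05 (Biostatistical considerations). Equal allocation (Randomization).

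**Input not in the protocol.** The correlation rho between the baseline scores, taken together, and readmission. It is assumed over 0.2 to 0.5.

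**The plan's own figure.** Per arm, n = [z_a √(2·0.4·0.6) + 0.842 √(0.25 + 0.21)]² / 0.2².
- Two-sided (z_a = 1.960): (1.358 + 0.571)² / 0.04 = 93.0, so 93 per arm, 186 in total; 206 with continuity correction.
- One-sided (z_a = 1.645): (1.140 + 0.571)² / 0.04 = 73.1, so 74 per arm, 148 in total. With continuity correction it is 83 per arm, **166 in total**.

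So 166 is reproduced only as a one-sided, continuity-corrected size. That mismatch with the two-tailed analysis is a separate issue. It matters here because it removes margin.

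**Unadjusted two-sided power.** Power = Φ{[0.2√n − 1.960·√0.48] / √0.46}.
- n = 83 per arm: (1.822 − 1.358) / 0.678 = 0.684, giving 75.3%.
- n = 100 per arm: (2.000 − 1.358) / 0.678 = 0.947, giving 82.8%.

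**Adjusted power.** Replace n by n/(1 − rho²). Example at rho 0.5: 83/0.75 = 110.7, so (2.104 − 1.358) / 0.678 = 1.100, giving 86.4%.

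| rho (assumed) | N = 166 | gain | N = 200 | gain |
|---|---|---|---|---|
| 0 | 75.3% | – | 82.8% | – |
| 0.2 | 77.0% | +2 | 84.3% | +2 |
| 0.3 | 79.2% | +4 | 86.2% | +3 |
| 0.4 | 82.4% | +7 | 88.8% | +6 |
| 0.5 | 86.4% | +11 | 92.0% | +9 |

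**Simulation check.** 5,000 trials per setting, chi-square against logistic regression with arm and one standardized covariate, marginal risks held at 50% and 30%.

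| Odds ratio per SD (assumed) | N = 166 | N = 200 |
|---|---|---|
| 1.00 | 75.7% to 75.5% | 83.5% to 83.2% |
| 1.65 | 76% to 78% | 84% to 85% |
| 2.23 | 76% to 80% | 83% to 87% |
| 3.32 | 75% to 84% | 84% to 91% |
| 4.95 | 74% to 88% | 83% to 93% |

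The first row shows that a useless covariate costs next to nothing. Under no effect at N = 200, the adjusted test rejected in 4.8% to 5.3% of trials and the unadjusted test in 5.7% to 5.8%.

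**Chance imbalance.** The difference in means of a standardized covariate has SD √(4/N): 0.155 at N = 166 and 0.141 at N = 200. A difference above 0.2 SD arises in about 20% and 16% of trials; above 0.3 SD in about 5% and 3%. At an assumed rho of 0.4 and 40% overall risk, a 0.3 SD imbalance moves the risk difference by 0.4·√(0.4·0.6)·0.3 = 0.059, about 6 of the planned 20 points.

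**The case against.** **The chi-square is a legitimate test.** This stands. Randomization makes it valid, and its error rate already allows for chance imbalance. A reader might infer that the planned test is biased or inflates type I error. Neither the protocol nor the calculation supports that.

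**Covariate choice is often left to the analysis plan.** True as a rule, and that plan is not shown. But this article does not stay silent: it names the between-arm tests, all unadjusted.

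**The multivariable analysis already adjusts.** Only in part. It does not say arm is excluded, and odds ratios are to be estimated. But its stated purpose is to explain associations with the outcome, it specifies no adjusted intervention effect, and its 12 variables are not limited to baseline values. They include non-compliance, while adherence is a secondary outcome that the intervention aims to change.

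**The variables are not shown to be prognostic.** This stands. A reader might infer that the protocol declares severity to be related to readmission. It lists severity as something to assess.

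**Not all the candidates are documented baseline data.** This stands. Entry scoring is documented for the Young and Hamilton scales. Polarity of the last episode and duration of previous episodes are not shown to be recorded at entry in both arms; the detailed first assessment form is described for the intervention arm.

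**The large gains need strong covariates.** This stands too. The gain reaches 5 points only at rho of about 0.34 (N = 166) or 0.37 (N = 200). The power figures also concern binary readmission, whereas Study outcomes defines the primary outcomes as counts, for which no gain was calculated.

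**Conclusion.** The point holds as an improvement in efficiency and balance, not as a fault in validity. The protocol fixes unadjusted between-arm tests for the outcome on which it is powered, collects two plausible severity covariates at entry, and does not stratify.

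The benefit is about 2 points of power if the scores are weakly prognostic and 9 to 11 if they are strongly so, from 75.3% at 166 patients and 82.8% at 200 with no losses. The upper figure should not be taken as the expected one, because nothing in the protocol locates rho within the range. What makes the change worthwhile is the asymmetry: a useful gain if the scores predict readmission, and practically no loss if they do not.

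**What to change.** In Biostatistical considerations:
- Make the primary between-arm analysis of readmission a logistic regression on randomized arm plus the baseline Young and Hamilton scores, both continuous. Fix this before the data are analysed.
- Add polarity of the last episode and duration of previous episodes only if both are recorded before randomization in all patients of both arms.
- Use the same baseline covariates in the model for the number of hospitalizations.
- Enter no adherence or severity measured after randomization.
- Report the standardized risk difference with its 95% CI, so that the target remains the 50% versus 30% contrast.
- Keep the chi-square as a sensitivity analysis. The explanatory multivariable analysis can stay as it is.

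**Cost.** No new patients, and no new data for the two scales. At 40% overall risk about 66 readmissions are expected among 166 patients (0.4·166) and 80 among 200 (0.4·200). That is enough for arm and up to four covariates, but not for all 12 listed variables. The small extra burdens are the standardization step after the regression, pooling over the multiple imputations planned under Missing data, and prespecifying the covariates. Trial status reports that recruitment is ongoing, so the change can still precede the analysis.

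### The protocol names two different tests, each without condition, for the between-group comparison of relapse events, one of its main end points

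*Protocol article*

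**What the plan says.** The conflict lies within one section of the protocol article, Biostatistical considerations.

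- **End points.** "The main end points of interest are the number and duration relapse events per person-year of follow-up and number of admissions" to hospital for bipolar disorder. These are counts, durations or rates.
- **Mann-Whitney, unconditional.** "The Mann-Whitney test will be used to compare outcomes between groups".
- **Student's t, unconditional.** "Mean number and duration of relapse events normalized to person-time, will be compared between groups using the Student’s t test".
- **General rule for continuous variables.** "for continuous variables by using the independent-sample t test (Mann-Whitney U test when appropriate"). No criterion for the switch is given. A further general sentence gives the independent-sample t test for comparing means between groups.
- **Proportions.** "The Pearson chi-square test (between study groups) and the McNemar test" are given for proportions, the first between groups and the second within groups.

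Three other places bear on the point. The outcomes section says "The primary outcomes to be measured are: (1) the number of hospitalizations; (2) the number of emergency service consultations", with unscheduled outpatient visits as the third. The Sample size calculation rests on a proportion: "Assuming readmissions will be 50% in the control group and 30% in the intervention group". The Abstract lists McNemar, chi-square and t tests and does not mention Mann-Whitney.

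**The concern.** Relapse events per person-year are an outcome compared between groups, so they fall under both unconditional sentences. Student's t compares mean rates and Mann-Whitney compares ranks. With skewed counts and many zeros, the two can give different answers from the same data. As the text stands, both P values follow the protocol, both are judged at 0.05, and nothing says which one decides. A borderline result could be called positive or negative according to which is reported. If significance on either is accepted, the error rate for that end point exceeds 5%.

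For hospitalizations, emergency consultations and unscheduled visits the position is weaker. No sentence ties Student's t to them by name; t and Mann-Whitney overlap there only through the general sentences.

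**Working it through.** **1. The scale on which the trial was sized.** The plan's figure is at least 166 patients for readmission of 50% versus 30% with 80% power. It reproduces as a comparison of two proportions with 1:1 allocation, one-sided 5% and continuity correction.

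- Uncorrected: n = [1.645·√(2·0.4·0.6) + 0.842·√(0.5·0.5 + 0.3·0.7)]² / 0.2² = (1.140 + 0.571)² / 0.04 ≈ 73.1 per arm.
- Corrected: (73.1/4)·[1 + √(1 + 4/(73.1·0.2))]² ≈ 82.8, so 83 per arm and 166 in total.

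The planned tests are two-tailed, which would give 93 per arm uncorrected. That is a separate matter. Here the result shows only that the sizing concerns a proportion, whereas the main end points are counts or rates.

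**2. Assumptions for the size of the conflict.** The documents give no mean or dispersion for any event count and no relapse proportion. The following are therefore assumed:

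- The 50% and 30% from the sample size section are taken as the proportion of patients with at least one event.
- Every patient has the same follow-up, so dividing by person-time changes nothing.
- Counts are Poisson, mean = −ln(1 − p), or negative binomial with size k, mean = k·[(1 − p)^(−1/k) − 1]. Dispersion is 1/k.

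The means at p = 0.5 and p = 0.3 are 0.69 and 0.36 (Poisson), 1.0 and 0.43 (k = 1), and 1.5 and 0.52 (k = 0.5).

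**3. Simulation.** There were 4,000 trials per setting, with two-sided tests at 0.05. Near a rate of 6% the simulation standard error is √(0.06·0.94/4000) ≈ 0.4 percentage points.

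**4. No effect (50% in both arms), 100 per arm.** The proportion with at least one test significant follows from the separate rates: P(either) = [P(t) + P(MW) + P(verdicts differ)] / 2.

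| Counts | t | Mann-Whitney | Verdicts differ | Either significant |
|---|---|---|---|---|
| Poisson | 5.03% | 4.98% | 2.40% | (5.03 + 4.98 + 2.40)/2 = 6.2% |
| k = 1 | 5.20% | 5.55% | 4.05% | (5.20 + 5.55 + 4.05)/2 = 7.4% |
| k = 0.5 | 4.48% | 4.62% | 4.50% | (4.48 + 4.62 + 4.50)/2 = 6.8% |

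Each test alone holds about 5%. Further runs with dispersion from 0 to 2 put the last column between 5.9% and 8.0%.

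**5. Sizing proportions (50% versus 30%).**

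| Counts | Power of t, 100 per arm | Power of Mann-Whitney, 100 per arm | Verdicts differ, 100 per arm | Verdicts differ, 83 per arm |
|---|---|---|---|---|
| Poisson | 91.4% | 88.6% | 4.7% | 6.2% |
| k = 1 | 96.2% | 91.8% | 5.5% | 8.0% |
| k = 0.5 | 98.3% | 92.6% | 6.2% | 8.4% |

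**6. Near the boundary.** Disagreement rises when the effect is smaller. With an assumed 50% versus 37%, the expected z for the proportions is 0.13 / √[(0.25 + 0.2331)/100] ≈ 1.9. The two tests then disagreed in 9 to 20% of trials at 100 per arm. The 37% is not in the documents and was chosen to sit at the boundary.

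**The case against.** The Mann-Whitney sentence directly follows the rule that allows that test for continuous variables where suitable, and may be only a loose continuation of it. One can also read the relapse sentence as a specific rule that overrides a general one. An analysis plan, not shown here, would commonly supply the rule for choosing a test, and the protocol says the statistical analysis will be blinded.

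Part of this stands. The lack of a selection rule alone would not be a finding, and blinding limits choosing a test to favour an arm. But the qualifier belongs to the preceding sentence and is not repeated. For quality of life the section does write out a rule (t if normal, otherwise rank-sum), so a conditional choice is stated where one was meant. Blinding does not say which P value decides.

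Two stronger readings are tempting and not supported:

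- **That Mann-Whitney is prescribed for every outcome.** The sentence speaks of outcomes, not all outcomes, and the quality-of-life rule shows that it is not universal.
- **That the same counts carry three rival tests, with chi-square as the third.** Chi-square is assigned to proportions and categorical variables. Its link to readmission is inferred from the sample size section, and it tests whether any event occurred, which is a different summary. Counting all three gives 8.0 to 9.2% false positives at 100 per arm in the runs above, but that figure does not measure the stated contradiction.

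**Conclusion.** The contradiction is real and narrow: two unconditional sentences give Mann-Whitney and Student's t for the same between-group comparison of relapse events, a stated main end point. For the three primary counts in the outcomes section, the two tests overlap only through general wording.

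The consequence is modest: about 6 to 8% false positives instead of 5% if either test may count, and opposite verdicts in about 5 to 6% of trials at 50% versus 30% with 100 per arm. The first figure applies only if whichever test is significant is accepted; the protocol does not say that it would be. Both rest on assumed count distributions, equal follow-up and event proportions borrowed from readmission. Duration of relapse was not simulated. The 9 to 20% disagreement near the boundary shows the direction and should not be read as the expected rate for this trial. The point deserves correction but does not invalidate the design.

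**What to change.** 1. Remove the unconditional Mann-Whitney sentence, or restrict it to named outcomes, so that it no longer conflicts with the t-test sentence on relapse events.
2. Before unblinding, name one deciding analysis for each main end point. If the proportion readmitted decides the trial, use chi-square or a risk difference with 95% confidence interval, which matches the sizing. If an event count or rate decides it, use one pre-specified method suited to skewed counts with person-time, for example a negative binomial model with log follow-up time as offset. Deleting the Mann-Whitney sentence alone would not be enough, since it would leave Student's t as the only unconditional test for such counts.
3. State that any other test of the same end point is a sensitivity analysis that cannot change the conclusion.

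The cost is a few sentences in the protocol or analysis plan, with no change to the sample size, data collection or patient procedures. The downside is that the team gives up choosing the test after seeing the distribution.
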